### Outcomes

#### Primary outcome measure

The primary outcome is a reduction in suicidal thoughts, measured by the Beck Scale for Suicide Ideation. The 19-item self-report scale measures the severity of suicidal thoughts on a scale from 0 to 38 with a higher score indicating higher severity. The Beck Scale for Suicide Ideation is a validated and frequently used measure of suicidal thoughts [12]. As in the Dutch trial, a pre-post difference of 6 points is considered clinically significant [8].

#### Secondary outcome measures

Secondary outcomes cover psychological wellbeing and health care utilization as well as productivity level for paid and unpaid work. In addition, episodes of deliberate self-harm, death by suicide and the participant’s perception and experience of the intervention will be measured.

Level of suicidal thoughts will be measured using the Suicidal Ideation Attributes Scale; a newly developed scale for measuring suicidal thoughts consisting of five questions [7]. We will test the validity of the Danish version of the scale.

Depressive symptoms will be measured using the Major Depression Inventory and the six-item Hamilton Depression Rating Scale. The Major Depression Inventory is developed by the World Health Organization’s Collaborating Center in Mental Health and will be used to generate an *International Classification of Diseases*, *10th edition* (ICD-10) or a *Diagnostic and Statistical Manual of Mental Disorders*, *version 4* (DSM-IV) diagnosis of clinical depression based on the baseline measurement [13, 14]. The six-item Hamilton Depression Rating Scale is an abbreviated version of the original 17-item scale containing six core symptoms of depression [15]. It will be used to assess the severity of a depression [16]. Hopelessness will be measured using an established standard tool, the Beck Hopelessness Scale [17]. The Penn State Worry Questionnaire Past Week will be used to determine the participants’ level of worrying [18]. Quality of life will be measured with the WHO-5 Well-Being Index, which is a well-established and validated questionnaire [19].

Health care utilization registered in the Danish registers will be assessed. Every person in Denmark has a personal identifier that is listed in the Danish registers [20]. Health care utilization at somatic hospitals, outpatient clinics and emergency rooms will be collected from the National Patient Register. Data on contacts to the participant’s general practitioner will, together with services from psychologists or psychiatrists who are subsidized or partly subsidized by the authorities, be obtained from the National Health Service Register. Data on prescribed medication will be obtained from the National Prescription Registry.

Level of paid and unpaid work will be assessed using the Trimbos/IMTA questionnaire for Costs associated with Psychiatric Illness [21].

Demographic data regarding age, sex, education level and relationship status will be collected through the Trimbos/IMTA questionnaire for Costs associated with Psychiatric Illness.

Information on deliberate self-harm episodes will be calculated using a self-report questionnaire and hospital records obtained from the Danish National Patient Register and the Psychiatric Central Research Register.

The participant will, after the intervention, be asked if they have experienced any negative effects related to the intervention and will be encouraged to give feedback; for instance, if they have not completed all six modules they will be asked why. Lastly, the participants will also be given the Internet Evaluation and Utility Questionnaire consisting of 15 questions regarding the usefulness, credibility and helpfulness of the intervention [22].

Data will be collected on how many times the participants log in to the website, how much time they spend on the intervention, how many modules they start and how many messages they send to the trial manager. The self-report questionnaires will be answered on the website. The SPIRIT figure (see Fig. 2) provides an overview of the measures used in the trial and their time points. See the Additional file 1 for the SPIRIT checklist.

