### Adverse events

Information on deaths by suicide or other causes of death will be acquired from the Cause of Death Register.

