### Statistical methods

The null-hypothesis assumption is that there is no difference between the intervention and the control condition with respect to suicidal thoughts and the secondary outcome measures. Linear mixed models with repeated measurements and an unstructured covariance matrix, will use measurements at baseline, 2, 4 and 6 weeks (post test) with the purpose of modeling changes over time in suicidal thoughts. Mixed models will also be used to assess the long-term effect at 6 months after post test as well as the effect on the participant’s level of depression. This analytical approach handles missing data appropriately using maximum likelihood, under the assumption that data are not missing-not-at-random. The analytical models will include baseline values and stratification variables. Changes in other secondary outcomes will be measured using ANCOVA with multiple imputations. The imputation models will be linear regression for scale variables and binary logistic regression for dichotomous variables. Imputation models will be constructed separately for each randomization group, and include baseline values of the scales in question, stratification variables, variables predicting missing data, and potential auxiliary variables identified for each outcome. Analytical models will include the stratification variables. Robustness of analyses using multiple imputations will be tested using sensitivity analyses instead, replacing missing data with either very low or very high scores for scale variables, and all 0s or all 1s for dichotomous data. Since no missing data are present for register data, imputations will not be necessary for these analyses. Cohen’s *d* test will be used to determine the difference between the intervention and the control condition. In addition, incidence rates of deliberate self-harm will be calculated using a self-report questionnaire and hospital records. A cost-effectiveness analysis will be conducted based on the health care utilization and productivity levels of the observed participants. Lastly, the participant’s evaluation, usage and experience of negative effects during the intervention will be calculated and described.

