### Sample size

The sample size was estimated based on the expected effect on suicidal thoughts at 6 weeks. In the Dutch trial, the pooled standard deviation at post test was 0.9 and an effect size of 0.28 (Cohen’s *d*) was observed. If the true difference in mean scores of the intervention and the control condition is 0.30 in the Danish trial, 175 participants in each condition are needed to reject the null hypothesis that there is no difference between the intervention and the control condition at post test on suicidal thoughts with probability (power) 0.8. The type I error probability associated with this test of the null hypothesis is 0.05.

Approximately 90% of participants in the Dutch trial completed all post-test questionnaires. Accounting for a dropout rate of 20%, a total of 438 participants will be needed.

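### The Adverse events section covers register deaths only; self-harm and worsening suicidal ideation, obtainable in both arms, should be named as harm outcomes and compared by arm

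*Protocol article*

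**What the plan says.** All references are to the protocol article.

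- **Adverse events.** The section is one sentence: "Information on deaths by suicide or other causes of death will be acquired from the Cause of Death Register".
- **Negative effects.** Under Secondary outcome measures: "The participant will, after the intervention, be asked if they have experienced any negative effects related to the intervention". Under Statistical methods, "the participant’s evaluation, usage and experience of negative effects during the intervention will be calculated and described". The Waiting list section gives controls no modules until 32 weeks have passed.
- **Deliberate self-harm.** It is a secondary outcome, drawn from a questionnaire and two national registers. Under Statistical methods, "incidence rates of deliberate self-harm will be calculated using a self-report questionnaire and hospital records". The same section says that register data have no missing values, and its null hypothesis covers the secondary outcomes as well as suicidal thoughts.
- **Suicidal thoughts.** The Abstract lists assessments in the trial at baseline and weeks 2, 4, 6 and 32. Under Primary outcome measure, "a pre-post difference of 6 points is considered clinically significant". Under Safety of subjects, a score of 27 or more in either arm leads to a telephone call. The stated analyses are linear mixed models of change to week 6, a mixed model for the 6-month effect, and Cohen's d.
- **Use of the result.** The Discussion says the program will be released free to everyone if its effect is not negative. The Background and Discussion say that people with severe suicidal thoughts, excluded from the Dutch trial, are included here.

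**The concern.** A trial that may lead to open release of a program for suicidal people needs at least one harm measure that compares the randomised arms and carries usable information. The two items that the protocol labels as harm do not do this. Deaths will be very few. The negative-effects question cannot be compared with a concurrent control, rests on self-attribution, and is answered only by those still responding.

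The data that could do the job are already planned: self-harm from registers and the Beck scale, in both arms. Neither is named as a harm outcome, and no comparison of the proportion who worsen is stated. If some participants deteriorate while the average improves, a model of mean change will report benefit and the Adverse events section will be silent.

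**Working it through.** **1. The plan's own figure.** Inputs from Sample size: "175 participants in each condition are needed to reject the null hypothesis", difference 0.30, power 0.8, type I error 0.05, dropout 20%. Sidedness is not stated; two-sided reproduces the figure.

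- n per arm = 2(1.960 + 0.842)² / 0.30² = 174.4, so 175.
- 175 / (1 − 0.20) = 218.75, so 219 per arm and 438 in total.

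This works if 0.30 is read as a standardised difference. How that fits the quoted standard deviation of 0.9 is a separate matter. Below, 219 per arm is used for all randomised participants and 175 for those expected to respond.

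**2. What deaths can show.** With 0 deaths in 219, the one-sided 95% upper limit is 1 − 0.05^(1/219) = 0.0136, or 1.4%. With no deaths in one arm, Fisher's exact test gives p = 0.061 for 5 in the other and p = 0.030 for 6, so at least 6 against 0 are needed for p < 0.05.

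The protocol gives no death rate, so the control risks below are assumptions. Power is exact Fisher, two-sided 0.05, 219 per arm.

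| Assumed control risk | Deaths expected if both arms have it (438 × risk) | Power, doubled risk | Power, five-fold risk |
|---|---|---|---|
| 0.1% | 0.4 | <0.1% | 0.1% |
| 0.25% | 1.1 | 0.05% | 3.6% |
| 0.5% | 2.2 | 0.9% | 23% |
| 1% | 4.4 | 5.3% | 62% |

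**3. Whether a mean can hide deterioration.** This is an illustration with assumed normal change scores, not a forecast.

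- Control: mean −3, SD 6. P(rise ≥ 6) = P(Z ≥ (6 + 3)/6) = P(Z ≥ 1.50) = 6.7%.
- Intervention: mean −4.7, SD 8. P(rise ≥ 6) = P(Z ≥ (6 + 4.7)/8) = P(Z ≥ 1.3375) = 9.1%.

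The intervention mean is better by 1.7 points, yet more participants worsen by 6 points. This needs a larger spread of change in the intervention arm; with equal spread, a better mean implies fewer worsening.

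**4. What a worsening comparison can show.** The control proportions are assumptions. Power is for two proportions, two-sided 0.05.

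| Assumed control proportion worsening | Rise detectable with 80% power, 219 per arm | Same, 175 per arm |
|---|---|---|
| 5% | 7.6 points | 8.7 points |
| 10% | 9.5 points | 10.8 points |
| 15% | 10.8 points | 12.2 points |
| 20% | 11.7 points | 13.2 points |

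A doubling from 10% to 20% would be seen with 84% power at 219 per arm and 75% at 175. As an interval, the 95% half-width for that difference is 1.96 × √[(0.10×0.90 + 0.20×0.80)/n], which is 6.6 points at n = 219 and 7.4 at n = 175.

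**5. Coverage of the two Beck outcomes.** The scale ends at 38, so a rise of 6 is impossible from a baseline above 32. A new score of 27 or more can occur only below 27 at baseline. Participants starting at 27 to 32 are covered by the first outcome only, and those above 32 by neither. Register self-harm covers everyone.

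**The case against.** The strongest reply is that harm is not confined to deaths and the question. Deliberate self-harm is a named outcome, its register part is available for all randomised participants, incidence rates are planned, and the null hypothesis extends to secondary outcomes. The mixed models would reveal a worse mean in the intervention arm, and high scores are followed up individually in both arms. Deterioration tables and counting rules are often left to an analysis plan, which is not shown.

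Most of this stands, and it limits the point. Four stronger readings are tempting, and the text does not support them:

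- *No stated harm measure compares the arms.* Self-harm rates can be compared; they are simply not designated as harm.
- *Self-report and hospital episodes are added together and so double counted.* The text says both sources are used and does not say that counts are summed.
- *The 6-point threshold applies only to benefit.* The sentence has no direction, and no 6-point responder analysis is planned either way.
- *The severe group has never been studied with this program.* The protocol says only that the Dutch trial excluded it.

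Nor should the 21% module completion in the Dutch trial be read as loss from harm assessment. About 90% in that trial completed the post-test questionnaires, and non-completers here are to be asked why they stopped.

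What the reply does not remove is that the Adverse events section, as written, has only deaths in it, and that no stated analysis would detect a deteriorating subgroup behind an improving mean. Following up individuals who score 27 or more is monitoring; it is not a comparison of arms.

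**Conclusion.** The point holds in this limited form. Adverse events are restricted to deaths, which at 219 per arm give a doubling at most about 5% power under assumed risks up to 1%, and an upper limit of 1.4% if none occur in an arm. The negative-effects question is uncontrolled and self-attributed. Self-harm is measured and its rates will be calculated, but it is not named as harm. Ideation is analysed as mean change only.

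A comparison of the proportion worsening would be considerably more informative, with a rise of about 8 to 13 points detectable with 80% power for control proportions of 5% to 20%. The rates are assumptions, because the protocol gives none. A fuller harm plan may exist in a document not shown. This is an inexpensive improvement and does not show that the planned efficacy analysis is wrong.

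**What to change.** Name the following as harm outcomes, compared by randomised arm with confidence intervals and without formal testing:

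- (a) a Beck scale increase of at least 6 points from baseline, at each of weeks 2, 4, 6 and 32;
- (b) a Beck score of 27 or more at any assessment after baseline, among those below 27 at baseline;
- (c) register-recorded deliberate self-harm from randomisation to week 32, in all randomised participants, before controls gain access.

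Report self-reported self-harm separately from register episodes. For (a) and (b), show missingness by arm, since these outcomes are lost with dropout, and handle missing scores with the imputation and extreme-value sensitivity approach already in Statistical methods. State how many participants start too high to register (a) or (b). Keep the negative-effects question as descriptive data, and keep deaths as planned.

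The cost is some analysis wording and a few descriptive tables. No new visits or instruments are needed, and the procedure for high scores is untouched. The downside is several more safety comparisons, some with wide intervals, which should be labelled descriptive.

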**Fig. 2 Fig2:**
[figure not shown]
Standard Protocol Items: Recommendations for Interventional Trials (SPIRIT) figure

### Adverse events

Information on deaths by suicide or other causes of death will be acquired from the Cause of Death Register.

### Statistical methods

The null-hypothesis assumption is that there is no difference between the intervention and the control condition with respect to suicidal thoughts and the secondary outcome measures. Linear mixed models with repeated measurements and an unstructured covariance matrix, will use measurements at baseline, 2, 4 and 6 weeks (post test) with the purpose of modeling changes over time in suicidal thoughts. Mixed models will also be used to assess the long-term effect at 6 months after post test as well as the effect on the participant’s level of depression. This analytical approach handles missing data appropriately using maximum likelihood, under the assumption that data are not missing-not-at-random. The analytical models will include baseline values and stratification variables. Changes in other secondary outcomes will be measured using ANCOVA with multiple imputations. The imputation models will be linear regression for scale variables and binary logistic regression for dichotomous variables. Imputation models will be constructed separately for each randomization group, and include baseline values of the scales in question, stratification variables, variables predicting missing data, and potential auxiliary variables identified for each outcome. Analytical models will include the stratification variables. Robustness of analyses using multiple imputations will be tested using sensitivity analyses instead, replacing missing data with either very low or very high scores for scale variables, and all 0s or all 1s for dichotomous data. Since no missing data are present for register data, imputations will not be necessary for these analyses. Cohen’s *d* test will be used to determine the difference between the intervention and the control condition. In addition, incidence rates of deliberate self-harm will be calculated using a self-report questionnaire and hospital records. A cost-effectiveness analysis will be conducted based on the health care utilization and productivity levels of the observed participants. Lastly, the participant’s evaluation, usage and experience of negative effects during the intervention will be calculated and described.

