## Methods and design

### Design

The SOS trial is designed as a randomized, controlled trial with a waiting-list control and with a 1:1 allocation ratio.

The primary hypothesis is that the intervention is superior to the control condition in reducing suicidal thoughts using the Beck Scale for Suicide Ideation at post test (6 weeks). Our secondary hypothesis is that the effect will be maintained at 6-month follow-up and that the program will be effective in improving the participant’s psychological wellbeing at post test and at follow-up. Table 1 shows the entries to the World Health Organization Trial Registration Data Set.

**Table 1 Tab1:** World Health Organization Trial Registration Data Set

Data category	Information
Primary registry and trial identifying number	ClinicalTrials.gov NCT02872610.
Date of registration in primary registry	18 August 2016
Secondary identifying number	TrygFonden 106690
	The Research Ethics Committee of the Capital Region of Denmark H-15002490
Source(s) of monetary or material support	TrygFonden reference number 106690
Primary sponsor	[name], Mental Health Centre Copenhagen
Contact for public queries	CM: [contact]
	MN: [contact]
	AE: [contact]
Contact for scientific queries	CM, MN, AE [contact]
	[contact]
	[contact]
	Mental Health Centre Copenhagen
Public title	The Self-help Online against Suicidal thoughts (SOS) trial – a Danish randomized controlled waiting-list trial for people with suicidal thoughts
Scientific title	The Self-help Online against Suicidal thoughts (SOS) trial – a Danish randomized controlled waiting-list trial for people with suicidal thoughts
Countries of recruitment	Denmark
Health condition(s) or problem(s) studied	Suicidal thoughts
Intevention(s)	An Internet-based self-help intervention for people with suicidal thoughts
	Waiting-list control condition
Key inclusion and exclusion criteria	Ages eligible for study: ≥18 years; sexes eligible for study: both
	Inclusion criteria: 18 years or older; sufficient command of the Danish language; have a personal code card (NemID)
	Exclusion criteria: no suicidal thoughts (defined as a cutoff score of <3 on the Beck Scale for Suicide Ideation)
Study type	Interventional
	Allocation: randomized
	Intervention model: parallel assignment
	Primary purpose: to lower the participant’s degree of suicidal thoughts
Date of first enrolment	August 2016
Target sample size	438
Recruitment status	Pending
Primary outcome(s)	Outcome: suicidal thoughts

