	Method of measurement: Beck Scale for Suicide Ideation
	Time point: 2, 4 and 6 weeks after baseline, with time × group interaction test as indicator of efficacy
Key secondary outcomes	Suicidal thoughts, depression, hopelessness, worrying, quality of life, health care utilization, medication prescriptions, production loss, episodes of deliberate self-harm, death by suicide, negative effects of the intervention and evaluation and utility of the self-help program

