### Randomization

After filling out the baseline questionnaires, the participants will be randomized to the intervention or control condition using a centralized and computer-based algorithm with a hidden sequence. The algorithm is not accessible or known to the researchers directly involved in the project. The randomization is stratified by sex and level of suicidal ideation (using a cutoff score of ≥16 points on the Beck Scale for Suicide Ideation). A 1:1 allocation ratio will be applied.

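### The primary mixed model appears to use baseline suicidal ideation as both response and covariate, and none of the available readings gives a baseline-adjusted test at week 6

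*Protocol article*

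**What the plan says.** Four places in the protocol article bear on the primary analysis.

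- **Statistical methods, model.** It specifies "Linear mixed models with repeated measurements and an unstructured covariance matrix", and these models "will use measurements at baseline, 2, 4 and 6 weeks (post test) with the purpose of modeling changes over time in suicidal thoughts". Baseline is therefore listed among the modelled measurements.
- **Statistical methods, adjustment.** "The analytical models will include baseline values and stratification variables". This sentence follows the mixed-model text and comes before the ANCOVA text. The ANCOVA and imputation text has its own later sentence on stratification variables.
- **Design, Table 1, primary outcome.** "Time point: 2, 4 and 6 weeks after baseline, with time × group interaction test as indicator of efficacy". Baseline is not among these time points.
- **Design, opening text.** The primary hypothesis is superiority on the BSS at post test, that is, at week 6.

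The article does not mention a baseline × time term, equal arm means at baseline, or leaving the covariate off the baseline row.

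**The concern.** If baseline is a response row and also a covariate on every row, the baseline response is regressed on itself. The model can fit that row perfectly, so the likelihood has no finite maximum and the software fails or returns a degenerate fit. In the simplest version of the model the covariate also drops out of the efficacy contrast, so the stated adjustment adjusts nothing.

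Two things are at stake in the primary analysis. One is the precision that baseline adjustment is meant to provide. The other is pre-specification: an analyst whose model does not converge must choose a repair with the data in hand, and the possible repairs give different estimates and standard errors.

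**Working it through.** **The plan's own figure.** For a two-sided 5% test with 80% power and a standardised difference of 0.30, n per arm = 2(1.960 + 0.842)²/0.30² ≈ 174.4, so 175 (power 80.1%). Then 350/0.8 = 437.5, so 438. Both figures in Sample size reproduce. They do so only if 0.30 is a standardised difference: a raw 0.30 with SD 0.9 would give 142 per arm. The calculation is a plain two-sample comparison at week 6 and assumes no gain from baseline adjustment.

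**Reading 1: baseline is both response and covariate.** Take time as categorical. Let D₀ and D₆ be the raw arm differences at baseline and week 6, and b a single baseline slope.

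- Arm effect at week 6: D₆ − bD₀
- Arm effect at baseline: D₀ − bD₀ = (1 − b)D₀
- Week-6 time × group contrast: (D₆ − bD₀) − (1 − b)D₀ = D₆ − D₀, whatever b is

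This was checked on one simulated complete dataset (350 participants, four visits; SD 1 and correlation 0.5 assumed), holding b fixed. Log-likelihoods are up to a constant.

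| b | log-likelihood | baseline residual variance | week-6 contrast |
|---|---|---|---|
| 0 | 207 | 0.936 | −0.1764 |
| 0.5 | 450 | 0.234 | −0.1764 |
| 0.9 | 1013 | 0.0094 | −0.1764 |
| 0.99 | 1819 | 9.4 × 10⁻⁵ | −0.1764 |
| 0.9999 | 3431 | 9.4 × 10⁻⁹ | −0.1764 |

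With b estimated freely, it ran to 0.999996 and the baseline residual variance fell to 1.7 × 10⁻¹¹. The log-likelihood rose by about 332 per iteration without settling (546, 879, 1211, … 4532).

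In the same data the raw change-score difference is −0.1764 (SE 0.1130) and ANCOVA gives −0.1873 (SE 0.0990). The variance ratio is (0.1130/0.0990)² ≈ 1.30.

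**Reading 2: baseline is a response only.** This is the row b = 0. The likelihood is well behaved, but the contrast is still D₆ − D₀, the change score.

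**Reading 3: baseline is a covariate only, with responses at weeks 2, 4 and 6 as in Table 1.** The interaction then tests whether D₄ − D₂ and D₆ − D₂ are zero. If D₂ = D₄ = D₆ = δ, both are zero for any δ. The test rejects at its 5% error rate however large the benefit, so it does not address superiority at week 6.

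**Size of the precision loss.** With equal variances over time and baseline-to-week-6 correlation r, the variance of the change score is proportional to 2(1 − r) and that of ANCOVA to 1 − r². The ratio is 2/(1 + r). Power for the week-6 contrast is Φ(0.30√(175/2)/f − 1.96), where f = √(2(1 − r)) for the change score and f = √(1 − r²) for ANCOVA. Here 0.30√87.5 = 2.806.

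| r (assumed) | variance ratio | power, change score | power, ANCOVA |
|---|---|---|---|
| 0.3 | 1.54 | 66% | 84% |
| 0.5 | 1.33 | 80% | 90% |
| 0.7 | 1.18 | 95% | 98% |

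These powers are for the single week-6 contrast, not for a joint interaction test over all visits.

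**Check of the repair.** Baseline as a covariate only, with the week-6 arm difference as the test, gives the ANCOVA result of −0.1873 (SE 0.0990). Baseline as a response with arm means constrained equal and no covariate gives −0.1873 (SE 0.0986).

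**The case against.** The strongest reply is that dual use is inferred. The article never labels baseline a response or a covariate. Its sentence on baseline values could simply restate that baseline is one of the measurements, and Table 1 supports a covariate-only model. A condensed article may also leave to an analysis plan which rows carry the covariate. It stands that dual use is a reading, though the plain one: baseline values are paired with stratification variables, which can only be covariates. The other two readings do avoid the degenerate fit, but Readings 2 and 3 above show that neither gives an adjusted week-6 test. The article fixes baseline's role inconsistently, which is different from leaving it open.

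A reader might also infer four stronger claims that the document does not support.

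- **Every dual-use model collapses to the change score.** This needs one baseline slope and free arm means at baseline. With a baseline × time term the point estimate returned to the ANCOVA value (−0.1873), and with equal baseline means the likelihood at fixed slopes also gave it. The covariance was singular or the fit unstable in these variants too, and the article states neither.
- **The trial is underpowered or 438 is wrong.** The sample size rests on an unadjusted week-6 comparison and reproduces. The change score falls below 80% only if r is under about 0.5, and no r is given.
- **The estimate is biased.** Under randomisation the change score is unbiased, and "The randomization is stratified by sex and level of suicidal ideation", which limits chance imbalance at baseline.
- **A time-constant BSS stratum effect distorts the later weeks.** In the dual-use fit the covariate already explains the baseline row, so no large stratum gap is left to carry forward. The stratum is also close to balanced between arms.

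A degenerate fit would also be obvious to the analyst. That limits silent error, but not the choice of repair after seeing the data.

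**Conclusion.** The point holds as a defect in how the primary model is specified. On the plain reading the model cannot be fitted by maximum likelihood. On the other two it either tests an unadjusted change score or does not test the week-6 hypothesis. The cost is precision and pre-specification, not validity. Against ANCOVA, the change score has 1.54 times the variance at r = 0.3 and 1.33 times at r = 0.5, about 18 and 10 percentage points of power at the planned effect and 175 per arm. These figures assume equal variances over time, complete data, categorical time, a two-sided 5% test and the stated values of r. The algebra and the degenerate likelihood do not depend on r.

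**What to change.** Use baseline once, in one of two ways:

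1. Responses at weeks 2, 4 and 6 with unstructured covariance, and fixed effects for arm × week, baseline BSS × week, sex and BSS stratum.
2. Baseline kept as a response, with arm means constrained equal at baseline and no baseline covariate.

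Deleting the covariate alone is not enough, because the free time × group contrast would still be the change score.

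Name the arm difference at week 6 as the primary test in place of the general time × group interaction. Align Table 1 and Statistical methods on baseline's role, and apply the same structure to the 32-week and depression models. The cost is a sentence or two of analysis wording. No extra data or participants are needed, and the sample size does not change.
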